### Data management

All protocol-required information collected during the trial must be entered by the investigator, or designated representative, in the eCRF. The investigator, or designated representative, should complete the eCRF as soon as possible after information is available, preferably on the same day that a trial subject is seen for a trial procedure. Any outstanding entries must be completed as soon as possible. The completed eCRF must be approved by the investigator or by a designated sub-investigator. The approved eCRF is then sent to IMBI for data management. To ensure that the database reflects the eCRFs correctly, the IMBI accomplishes a double entry of data to the statistical program SAS. IMBI representatives will check completeness, validity, and plausibility of data using validating programs that generate queries when indicated. All validation rules will be predefined in a data validation plan. The investigator or the designated representatives are obliged to clarify or explain the queries. If no further corrections are to be made in the database, it will be closed and used for statistical analysis. The data will be managed and analyzed according to the appropriate standard operation procedure (SOPs) valid in the IMBI. For additional health economic analyses, IMBI and all participating health insurance companies will provide the Chair of Health Economics and Health Care Management, Bielefeld University, with pseudonymized eCRF and health insurance data via a special trust agency. Apart from health economic aspects, the Chair of Health Economics and Health Care Management, Bielefeld University, will assess the QoL of all participating patients using the VR-36 questionnaire [13]. According to §13 of the GCP Ordinance [19], all important trial documents (e.g., CRFs) are archived for at least 10 years after completion of the clinical trial.

### Statistical methods

The primary hypothesis will be analyzed using Mann-Whitney *U* test. Primary analysis will include all randomized patients (intention to treat (ITT)-population). Although DOOR/RADAR score values can be calculated reliably, any missing data will be replaced with multiple imputation methods [20]. The imputation model will be based on the variables age, SOFA score at sepsis onset, and survival and furthermore assumes that missing values of the primary endpoint are “missing at random”. Accordingly, missing values can be estimated by relevant co-variables in the imputation model. In order to review the assumptions of the imputation model, sensitivity analyses as well as “best case” and “worst case” scenarios will be performed. Moreover, these cases will be analyzed without the missing variables (complete case analysis). The primary endpoint will additionally be analyzed in a dichotomous way (good vs. bad outcome: e.g., OCO 1 versus OCO 2-5) using a logistic regression model, including group membership (CG, IG) and additional confounders (e.g., age, sex, SOFA score, comorbidities) as co-variates. The primary as well as all secondary endpoints will be presented using descriptive statistical methods. Moreover, 95% confidence intervals as well as descriptive *p* values for the effect estimates will be reported. In addition, mortality at 90 and 180 days will be evaluated using methods for survival-time analyses (Kaplan-Meier, Cox-proportional-Hazards-Regression). Wherever possible, graphs are used for visualization. All statistical tests will be performed using SAS (SAS Institute, Cary, NC). A *p* value of < 0.05 will be considered statistically significant. Detailed information of all statistical methods will be summarized and refined in a detailed statistical analytic plan (SAP).

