### Randomization process and interventions

Eligible patients will be randomized (1:1) into one of the two different study arms (CG, control group/IG, intervention group) using block randomization with randomized block length. The randomization is done stratified by study center using an internet-based tool (URL: www.randomizer.at). The randomization is blinded for the patient, blinding of the attended physician is not possible. All included patients will be treated according to current sepsis guidelines [3, 4]. Pathogen diagnostics in patients of the CG will be done with standard-of-care microbiological analyses followed by optional expert consultations, whereas in patients of the IG, a comprehensive concept of digital precision diagnostics (including NGS-based diagnostics, standard-of-care microbiological analyses, and optional expert consultations) will be provided.

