### Participant timeline, data collection, and sample handling

#### Data collection

As part of the study, patients´ baseline data is collected once at the time of sepsis diagnosis (= baseline): patient demographics (e.g., age, sex), date and time of hospital and ICU admission, admission source (e.g., emergency department, outpatient clinic/referral, operating room, post-anesthesia care unit, and other hospital units), major comorbid conditions, immune status (host factors predisposing for an immunodeficiency according to [12]; Supplemental File 2), site of suspected or confirmed infection, antimicrobial course prior to study enrolment, surgery/procedures for suspected site of infection prior to enrolment, and Sequential Organ Failure Assessment (SOFA) score (Supplemental File 3). Clinical data collection is carried out at the time of sepsis diagnosis (= baseline), 3, 7, 14, and 28 days later. All laboratory parameters will be measured according to the local standard. The outcome evaluation takes place 28 days after the onset of sepsis. Clinical data collection during admission will include pertinent laboratory data, use of mechanical ventilation, and antimicrobial/antibiotic therapy including duration of therapy, and date therapy will be initiated and discontinued. Vasoactive drug therapy, renal replacement therapy, surgical and other procedures for diagnosis/treatment of infection, radiological testing for diagnosis/evaluation of potential infection, indwelling vascular access devices, and vital status will also be recorded. Discharge data will include the date of discharge (ICU/IMC, and hospital), discharge destination (general hospital ward, skilled nursing facility, and home), and vital status at discharge (survival/death). Finally, quality of life (QoL) of all participating patients will be assessed at onset, 90 and 180 days after sepsis onset using the VR-36 questionnaire [13].

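### The primary Mann-Whitney test is valid and adequately powered as planned, but it leaves unused the baseline SOFA, age and centre information that could sharpen it at no cost in patients

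*Protocol article*

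**What the plan says.** Under Statistical methods the protocol article fixes the primary test: "The primary hypothesis will be analyzed using Mann-Whitney" U test, in all randomised patients. It names no stratum and no covariate. Under Randomization process and interventions, allocation is 1:1 and blocked, and "The randomization is done stratified by study center using an internet-based tool". Under Data collection, the baseline data include "patient demographics (e.g., age, sex), date and time of hospital and ICU admission", and further on "and Sequential Organ Failure Assessment (SOFA) score".

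Statistical methods then uses these variables twice outside the primary test. For missing primary endpoint values, "The imputation model will be based on the variables age, SOFA score at sepsis onset, and survival". In an additional logistic regression of a dichotomised outcome, with OCO 1 against OCO 2 to 5 as the example, the model takes group and "additional confounders (e.g., age, sex, SOFA score, comorbidities) as co-variates". Centre is not in that example list. The section closes by leaving refinement of the methods to an SAP, which is not shown.

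**The concern.** The protocol presumes that SOFA and age carry information about the DOOR-RADAR score, since it would fill in missing scores from them, yet the test that decides the trial ignores them. It also ignores the one factor that structures the randomisation. When baseline variables predict the outcome, an unadjusted comparison keeps their variance in the error term. When the stratification factor predicts the outcome, a test that ignores it is somewhat conservative.

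At stake is power that could be had without recruiting anyone, and it matters more if the true effect is smaller than planned. The supportive logistic model does not fill the gap: it is not the primary test, it collapses the ranking to two classes, and it drops the anti-infective duration part of the score.

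**Working it through.** **Inputs from the protocol article.** Relative effect 0.6, 90% power with 180 per arm, 12.5% drop-out, 410 in total, and 28% in OCO 5 (Sample size calculation); significance level 0.05 (Statistical methods); 1:1 allocation (Randomization process and interventions).

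**Assumptions, not in the document.** Two-sided testing; R², the share of rank variance explained by the adjustment variables, from 0.05 to 0.20; a relative effect of 0.58 as an illustration of a smaller effect; for the simulation, 20 centres of equal size.

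**Step 1: reproduce the plan.** Noether's formula for the Mann-Whitney test is N = (z₀.₉₇₅ + z₀.₉₀)² / [12 × 0.25 × (p − 0.5)²].

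- N = (1.960 + 1.282)² / (3 × 0.1²) = 350.2, or 176 per arm, against 180 stated.
- Power with 360 patients = Φ(√(360 × 3) × 0.1 − 1.960) = Φ(1.326) = 90.8%.
- With a tie factor for the 28% deaths, 1 − 0.28³ = 0.978, N is 343 and power is 91.4%.
- A one-sided test would need only 143 per arm, so the plan fits a two-sided test.
- Drop-out: 180 / 0.875 = 205.7, against 205 stated.

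The plan's figures reproduce.

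**Step 2: effect of adjustment.** A rank-based adjusted test multiplies the error variance by (1 − R²), so power = Φ(√(360 × 3 / (1 − R²)) × (p − 0.5) − 1.960). The equivalent gain in sample size is 1/(1 − R²) − 1.

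| R² (assumed) | Power at 0.60 | Power at 0.58 | N for 90% power at 0.60 | Equivalent gain in N |
|---|---|---|---|---|
| 0 (plan) | 90.8% | 74.8% | 351 | 0% |
| 0.05 | 92.1% | 77.0% | 333 | 5% |
| 0.10 | 93.4% | 79.1% | 316 | 11% |
| 0.20 | 95.7% | 83.6% | 281 | 25% |

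**Step 3: simulation.** There were 1,500 trials per scenario, each with 360 patients, centre-balanced allocation and the worst 28% tied, and an effect set to a relative effect of 0.6 before tying. Van Elteren is the centre-stratified rank test without covariates. Shares are on the latent scale.

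| Centre share | Covariate R² | Plain test | Van Elteren | Rank ANCOVA, centre + covariate |
|---|---|---|---|---|
| 0.02 | 0.10 | 91.7% | 89.7% | 94.7% |
| 0.05 | 0.10 | 91.3% | 90.9% | 94.5% |
| 0.05 | 0.20 | 91.0% | 90.8% | 96.1% |
| 0.10 | 0.20 | 92.9% | 93.4% | 97.8% |

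Stratifying by centre alone gives no clear gain; adding the covariate does. Under no effect, rank ANCOVA rejected in 4.4% to 5.8% of trials. The Monte Carlo standard error at 5% is √(0.05 × 0.95 / 1500) = 0.56 points, so this is compatible with 5%.

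**Step 4: conservatism from ignoring centre.** If arms are balanced within centres and centre explains a share c of the variance, the plain test's true level is about 2[1 − Φ(1.960 / √(1 − c))]. At c = 0.05 this is 2[1 − Φ(2.011)] = 4.4%. The simulated level was about 4.5% in every scenario, including the one with no centre effect, so the simulation does not separate this small loss from noise.

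**The case against.** The strongest defence is that the plan is coherent. Its target, under Primary outcomes, is the probability that an intervention patient has a lower score than a control patient. The sample size is built on that quantity, and the Mann-Whitney test is its natural test. Level and power are as stated. A reader might infer from the missing covariates that the trial is underpowered or the test invalid; step 1 shows that the documents support neither. This part of the defence stands.

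A reader might also infer that ignoring the stratification factor is a serious fault in itself. The calculations do not bear that out: the loss of level is slight, and centre stratification alone adds almost nothing. The document gives no number of centres and no centre effect.

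The size of the gain follows from the assumed R². The protocol treats SOFA and age as predictive but does not say how strongly, so no single figure for patients saved can be read from it. Nor was interval width computed, so no claim about it is made here.

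It may also be said that the unseen SAP could deal with adjustment. Covariate handling often sits there, but here the primary test is already named in the protocol, so moving to an adjusted test would be a change to it and not the filling of a gap.

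**Conclusion.** The point holds as one of efficiency. The planned test is valid and meets its 90% power, but it passes over baseline predictors that the trial collects and that its own imputation model relies on. At an assumed R² of 0.05 to 0.20, adjustment adds about 1 to 5 percentage points of power at a relative effect of 0.6, and about 2 to 9 points at 0.58. If SOFA and age predict the ranks less well than this, the gain is smaller. The change is worth making because it needs no new data; the trial is not unsound without it.

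**What to change.** Before any outcome data by arm are seen, name as the primary test a rank ANCOVA of the DOOR-RADAR score on arm, stratified by centre and adjusted for baseline SOFA and age, with a rule fixed in advance for pooling small centres. Timing matters because the Discussion says that the statisticians will not be blinded, and the covariate list in the logistic model is only illustrative, so it cannot serve as pre-specification.

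Keep the marginal probability that an intervention patient's score is lower than a control patient's as the estimand. Rank ANCOVA supplies the test but does not itself estimate that probability, so report it with a 95% confidence interval from a covariate-adjusted, standardised estimator. A probabilistic index model reported conditionally on covariates would answer a different question from the one the trial was sized for. Run the analysis in each imputed dataset and combine the results. Keep the unadjusted Mann-Whitney test as a sensitivity analysis.

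The cost is programming and a documented change to protocol and SAP. Under Protocol amendments, that means approval by the signatories and a positive ethics assessment. No new data are needed.

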### Outcomes

#### Primary outcomes

*DigiSep* primarily evaluates whether the so-called DOOR-RADAR (Desirability of Outcome Ranking/Response Adjusted for Duration of Antibiotic Risk) score can be significantly improved by application of an additional NGS-based diagnostic concept [14] (Table 2).

**Table 2 Tab2:** Primary and secondary outcomes of *DigiSep*-trial

Outcomes	Data source	Timepoint/frame
Primary outcomes		
DOOR/RADAR score	eCRF	28 days
Secondary outcomes		
Long term mortality	Statutory health insurance data, eCRF	90, 180 days
Degree of organ dysfunction/failure: • Duration of mechanical ventilation • Length of time until shock resolution • Ongoing RRT-dependency	eCRF	28, 90, 180 days
Hospital length of stay	Statutory health insurance data, eCRF	28, 90, 180 days
Cumulative need for anti-infective drugs	Statutory health insurance data, eCRF	28, 90, 180 days
Beginning of a targeted anti-infective treatment regimen	eCRF	28 days
Resource utilization (outpatient and inpatient)	Statutory health insurance data	28, 90, 180 days
Duration and costs of incapacity to work	Statutory health insurance data	28, 90, 180 days
Direct medical costs (outpatient and inpatient)	Statutory health insurance data	28, 90, 180 days
Quality-of-life (QoL)	VR-36 questionnaire	0, 90, 180 days

Abbreviations: *RRT* renal replacement therapy; *QoL* quality of life; *eCRF* electronic case report from; *DOOR/RADAR score* Desirability of Outcome Ranking/Response Adjusted for Duration of Antibiotic Risk score

The DOOR-RADAR score represents a combined clinical endpoint. While the DOOR component reflects the overall clinical outcome (OCO) consisting of intensive/intermediate care unit length of stay (ICU/IMC-LOS), mortality, and RRT-dependent AKI, the RADAR component reflects the duration of anti-infective treatment. Both components are combined to yield the DOOR-RADAR score, which is a numerical value and calculated as follows:
$$ \mathrm{DOOR}-\mathrm{RADAR}\ \mathrm{score}\ \left\{\begin{array}{c}=\mathrm{OCO}+\left[\frac{\mathrm{number}\ \mathrm{of}\ \mathrm{days}\ \mathrm{with}\ \mathrm{anti}-\mathrm{infective}\ \mathrm{treatment}\kern0.5em }{\max .\kern0.5em \mathrm{number}\ \mathrm{of}\ \mathrm{days}\ \mathrm{with}\ \mathrm{anti}-\mathrm{infective}\ \mathrm{treatment}\kern0.5em +1\ \mathrm{day}}\right],\mathrm{if}\ \mathrm{OCO}\le 4\\ {}=5\kern28em ,\mathrm{if}\ \mathrm{OCO}=5\end{array}\right. $$

with the OCO being calculated as

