### Sample size calculation

For sample size calculation, a sophisticated secondary outcome analysis of the following four large sepsis studies of the SepNet Study Group (VISEP [15], MAXSEP [16], HYPRESS [17], and SISPCT [18]) was performed, in which the above described OCO-groups were represented as follows: OCO 1: 33%, OCO 2: 3%, OCO 3: 22%, OCO 4: 14%, and OCO 5: 28%. It is assumed that the anti-infective treatment period in OCO 1 and OCO 2 is 7 days in average, whereas it is prolonged up to 15 days (with a standard deviation of 10 days) in average in OCO 3 and OCO 4. Based on the assumption that the OCO group can be improved by at least 2 stages in 42% of IG patients in parallel to a shortening of the anti-infective treatment by 2 days, this would result in a power of 90% with 180 patients in each of the two study groups (CG, IG), provided that an IG patient has a lower DOOR/RADAR score as compared to a CG patient with a relative effect of *p* = 0.6. Including an additional drop-out rate of 12.5% (and considering these patients as OCO 5) would finally result in an overall sample size of 410 patients (CG: *n* = 205/IG: *n* = 205).

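### The imputation model for the primary endpoint omits randomised arm, so any effect not carried by survival is diluted towards 0.5 in proportion to the share of missing scores

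*Protocol article*

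**What the plan says.** Under Statistical methods, the test is fixed: "The primary hypothesis will be analyzed using Mann-Whitney *U* test". It is applied to all randomised patients. The section expects that scores can be calculated reliably, but adds that "any missing data will be replaced with multiple imputation methods", assuming that missing values of the primary endpoint are missing at random. The predictors are then listed: "The imputation model will be based on the variables age, SOFA score at sepsis onset, and survival". Imputation by arm is not mentioned anywhere in the article.

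The same section does name the arm for the supportive logistic regression, "including group membership (CG, IG) and additional confounders". Best-case, worst-case and complete-case analyses are planned as sensitivity analyses. Details are left to a SAP that is not shown.

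Under Primary outcomes, a death within 28 days has a score of exactly 5. A survivor's score is the OCO category (1 to 4, set by ICU/IMC stay and RRT-dependent AKI) plus a fraction for anti-infective days.

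**The concern.** An imputation model should contain the variable whose effect the analysis then estimates. If arm is left out, missing scores in both arms are drawn from one distribution, given the listed predictors. Age and baseline SOFA are balanced by randomisation and cannot carry a treatment effect. Survival is a post-randomisation outcome and can, but only the mortality part.

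The rest of what the trial hopes to change (stay, RRT-dependent AKI, anti-infective days) separates patients only within OCO 1 to 4, that is, among survivors. For an imputed survivor, that part of the arm difference is averaged away. At stake is a primary estimate that is too close to no difference, in a trial sized for a modest effect.

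**Working it through.** **Inputs from the protocol.** Relative effect: "with a relative effect of *p* = 0.6". Power: "this would result in a power of 90% with 180 patients in each of the two study groups". Alpha: "A *p* value of < 0.05 will be considered statistically significant" (sidedness not stated). Drop-out 12.5%, total 410. OCO distribution 33/3/22/14/28%. Planned gain: at least two OCO stages in 42% of IG patients, with treatment 2 days shorter.

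**1. The plan's own figure.** By Noether's formula for the Mann-Whitney test, two-sided:

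N = (1.960 + 1.282)² / (12 × 0.25 × 0.1²) = 10.507 / 0.03 = 350.2, so 176 per arm against the stated 180.

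The one-sided version gives 143 per arm and does not reproduce. Power at 180 per arm is Φ(√(3 × 360) × 0.1 − 1.960) = Φ(1.326) = 90.8%. Inflation gives 360 / 0.875 = 411.4, so 412 against the stated 410. The plan reproduces. At 410 patients with nothing missing, power is Φ(√1230 × 0.1 − 1.960) = 93.9%.

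**2. Upper bound of attenuation.** Let a fraction m of scores in each arm be drawn from the pooled distribution, with 1:1 allocation and missingness independent of arm. The completed distributions are

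G_I = (1 − m/2) F_I + (m/2) F_C, and G_C with the roles exchanged.

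Then p_est − 0.5 = [(1 − m/2)² − (m/2)²] (p − 0.5) = (1 − m)(p − 0.5).

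For m = 0.125: 0.5 + 0.875 × 0.1 = 0.5875.

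**3. Survival known and in the model.** A simulation with 400,000 patients per arm used the protocol's OCO distribution. The 42% two-stage gain was applied to every OCO group, which lowers IG deaths from 28% to 0.58 × 28% = 16.2%. Days averaged 7 (SD 7, my assumption because none is stated) in OCO 1–2 and 15 (SD 10) in OCO 3–4, less 2 days in IG. The full-data relative effect was 0.619, near the planned 0.6. Known deaths kept the score 5, and missing survivor scores were drawn pooled over arms. At 12.5% missing the estimate was 0.6117 against 0.6189, so (0.1117 / 0.1189) = 94% of the effect was kept. Scaled to 0.6 this is 0.5 + 0.94 × 0.1 = 0.594. Drawing within arm gave 0.619, with no attenuation.

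| Assumed share missing | Survival known: simulated (full data 0.619) | Survival known: scaled to 0.6 | Upper bound for true 0.6 | Power at upper bound, N = 410 |
|---|---|---|---|---|
| 2% | 0.618 | 0.599 | 0.598 | 93.0% |
| 5% | 0.616 | 0.598 | 0.595 | 91.5% |
| 12.5% | 0.612 | 0.594 | 0.5875 | 86.6% |
| 20% | 0.608 | 0.591 | 0.580 | 80.1% |

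**4. If the arms differ only among survivors.** The full-data effect is then 0.5685. At 12.5% missing it becomes 0.560, so 0.060 / 0.0685 = 88% is kept even with survival known. This is the upper-bound factor of step 2.

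**5. Power against a fair comparator.** At 12.5% missing and N = 410:

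- estimate 0.594: Φ(35.07 × 0.094 − 1.960) = 90.9%
- estimate 0.5875: Φ(35.07 × 0.0875 − 1.960) = 86.6%
- complete cases, 0.875 × 410 ≈ 359 patients, effect 0.6: Φ(√1077 × 0.1 − 1.960) = 90.7%

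The first two ignore between-imputation variance and so flatter the imputed analysis.

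**The case against.** The strongest reply is that the article only says what the model is based on and defers refinement to a SAP, which could impute within arm without adding a covariate. That is possible. But the article gives a specific list that lacks the tested variable, while naming arm for the logistic model in the same section. A SAP that follows the list repeats the omission. The complete-case analysis would help to reveal the dilution, but only as a sensitivity analysis.

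Other objections stand and limit the point. Four stronger readings are tempting and are not supported:

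- **Imputed scores carry no treatment effect at all.** Survival is in the model and separates OCO 5 from OCO 1–4, so a mortality effect is transmitted.
- **Omitting arm costs power from 94% to 87%.** The 87% is the upper bound, and the 94% assumes no missing data. A complete-case analysis at 12.5% missing also falls to about 91%. Moreover, 12.5% is a drop-out rate, with those patients counted as OCO 5 in planning. It is not a forecast of missing scores.
- **Only the composite is imputed, so survivors could receive a 5.** The article fixes neither the level nor the algorithm of imputation. The statement "Both components are combined to yield the DOOR-RADAR score, which is a numerical value" defines the score and says nothing on imputation.
- **Centre must be in the model.** The planned test is not stratified by centre, so its absence does not create the same mismatch.

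**Conclusion.** The point holds in a limited form. The stated imputation model omits the randomised arm, and following it biases the primary estimate towards 0.5. The loss lies between none (no missing scores, or an effect wholly carried by known survival) and a factor of 1 − m. It is closer to the latter the less the treatment acts through mortality; the 94% retained in step 3 depends on a planning scenario with a large mortality gain.

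The bias does not inflate type I error. At a few per cent missing it is negligible in practice; at 12.5% it could take power below the planned 90%. These sizes assume missingness independent of arm, mortality and survivor effects in the same direction, the SD of 7 days in OCO 1–2, and the Noether variance. The missing share is an assumption throughout.

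**What to change.** State in the SAP that randomised arm is a predictor in the imputation model, or that imputation is done separately by arm. State also that the score is computed as 5 for every known death, following the protocol's own formula, so that these patients are never imputed. Imputing missing components (stay, RRT, anti-infective days) and then computing the score is a sensible option, since it uses whatever is observed, but it is not needed to remove this bias.

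The cost is SAP wording and programming, settled before the database is closed. No design change, further patients or new data are needed.

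### The supportive adjusted analysis of clinical outcome is dichotomous, and the only cut named (OCO 1 versus 2-5) discards much of the improvement that the sample size assumes; a five-level ordinal model would keep it

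*Protocol article*

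**What the plan says.** All points are in the Methods of the protocol article.

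- **Statistical methods.** The primary hypothesis is tested by Mann-Whitney on the full DOOR-RADAR score. Then: "The primary endpoint will additionally be analyzed in a dichotomous way (good vs. bad outcome: e.g., OCO 1 versus OCO 2-5"), by logistic regression with arm and covariates; age, sex, SOFA score and comorbidities are given as examples. No other model has named covariates. Cox regression is planned for 90- and 180-day mortality. P values for effect estimates are called descriptive, and details are left to a SAP that is not shown. On the threshold: "value of < 0.05 will be considered statistically significant".
- **Primary outcomes.** OCO ranks five states: survivors with a short stay, without (1) or with (2) renal replacement; survivors with a long stay, without (3) or with (4) renal replacement; and death (5). Anti-infective days add a fraction below 1 to levels 1 to 4.
- **Sample size calculation.** The control distribution is "OCO 1: 33%, OCO 2: 3%, OCO 3: 22%, OCO 4: 14%, and OCO 5: 28"%. The effect is that "the OCO group can be improved by at least 2 stages in 42% of IG patients". The second part of the assumption concerns treatment duration and reads "in parallel to a shortening of the anti-infective treatment by 2 days". The stated result: "this would result in a power of 90% with 180 patients in each of the two study groups". It is conditional on the size of the effect: "provided that an IG patient has a lower DOOR/RADAR score as compared to a CG patient with a relative effect of *p* = 0.6". A 12.5% dropout rate, counted as OCO 5, raises this to 205 per arm.

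**The concern.** The dichotomous form is stated; only the choice of cut is left open, and just one cut is given. That cut counts a patient as improved only on reaching OCO 1. The trial is planned on improvements of two stages or more, and of the exact two-stage moves (3 to 1, 4 to 2, 5 to 3) only the first reaches OCO 1.

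At stake is the value of the supportive analysis. The primary score mixes OCO with anti-infective days in an open-label trial, so readers will ask whether a favourable result reflects patient outcome. The logistic model is the only one described that takes OCO alone as its outcome. If it misses most of the planned effect, it may well look negative beside a positive primary test even when the effect is real.

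**Working it through.** **Inputs** (Sample size calculation, unless noted): control OCO 33/3/22/14/28%; 42% improving by at least two stages; treatment 2 days shorter; relative effect 0.6; 90% power; 180 per arm, 205 after 12.5% dropout; alpha 0.05 (Statistical methods). Two-sided testing is assumed.

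**1. The plan's own figure.** Noether's formula for 1:1 allocation: N = (1.960 + 1.282)² / [12 × 0.25 × (0.6 − 0.5)²] = 350.2, or 175.1 per arm, rounded up to 176. The plan has 180, where power is 90.8%. Dropout: 180 / 0.875 = 205.7, against 205 stated. The plan's figures are reproduced closely.

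**2. The planning scenario.** Move 42% of OCO 3, 4 and 5 by exactly two stages:

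| Move | Share of arm | Crosses OCO 1 vs 2-5? |
|---|---|---|
| 3 to 1 | 0.42 × 22% = 9.24% | yes |
| 4 to 2 | 0.42 × 14% = 5.88% | no |
| 5 to 3 | 0.42 × 28% = 11.76% | no |
| Total | 26.88% | 9.24 / 26.88 = 34.4% |

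The intervention distribution becomes 42.24/8.88/24.52/8.12/16.24%. With treatment 2 days shorter, simulation gives a relative effect of 0.603 on the DOOR-RADAR score if the duration SD is 10 days throughout, and 0.621 if it is 3 days in OCO 1-2 (the document gives 10 days only for OCO 3-4). This agrees with the stated 0.6.

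So 17.64 of 26.88 points (65.6%) are invisible to the cut. In 205 patients that is 0.1764 × 205 ≈ 36 of 0.2688 × 205 ≈ 55 improved patients, including all 0.1176 × 205 ≈ 24 averted deaths.

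**3. Power of the named cut, 205 per arm.** OCO 1 is 33.0% vs 42.24%, mean 0.3762.
Φ{[0.0924√205 − 1.960√(2 × 0.3762 × 0.6238)] / √(0.33 × 0.67 + 0.4224 × 0.5776)} = Φ{(1.323 − 1.343) / 0.682} = 49%. Simulated logistic regression gives 48.5%.

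**4. Power of an ordinal analysis of OCO, 205 per arm.** The relative effect on OCO alone is 0.592. With p̄ the mean category proportions of the two arms, the tie-corrected null standard error is √[(1 − Σp̄³)(2n + 1) / (12n²)] = √[0.9218 × 411 / (12 × 205²)] = 0.0274. Power = Φ(0.092 / 0.0274 − 1.960) = 92%. A simulated proportional-odds model also gives 92%.

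**5. The four cuts in this scenario, 205 per arm.**

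| Cut | Odds ratio | Power |
|---|---|---|
| 1 vs 2-5 | 1.49 | 49% |
| 1-2 vs 3-5 | 1.86 | 87% |
| 1-3 vs 4-5 | 2.25 | 97% |
| 1-4 vs 5 | 2.01 | 82% |

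**6. Other sample sizes and readings.**

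| Scenario | OCO 1 vs 2-5 | Ordinal OCO |
|---|---|---|
| As above, 180 per arm | 44% | 88% |
| As above, 205 per arm, 12.5% dropouts as OCO 5 | 41% | 80% (simulated 82%) |
| 42% of all intervention patients move two stages (42/64 = 65.6% of OCO 3-5) | 85% | over 99% |
| A quarter of OCO 4-5 movers reach OCO 1 | 81% | 97% |
| Half of OCO 4-5 movers reach OCO 1 | 96% | 99% |

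The last three rows are at 205 per arm without dropouts. The third scenario implies a relative effect of about 0.66 on the full score (SD 10 days), above the stated 0.6, and still leaves two thirds of improvements uncounted. In the fourth, 51% of improvements cross the cut. In the fifth, the gap is small and survival versus death (82%) becomes the weaker cut. If every such mover reached OCO 1, both analyses would exceed 99%.

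**The case against.** The case for leaving the plan alone is fair in several respects.

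- **The analysis is supplementary.** The Mann-Whitney test on the full score decides the trial and is untouched. This stands, and it limits the weight of the point.
- **Cut and covariates are examples, and a SAP will refine them.** This stands for the cut. The dichotomous form, however, is stated in the protocol itself. A reader might infer that unblinded statisticians could pick the best cut after seeing the data. The documents do not support this: nothing says that the SAP will leave the cut open, and the p values are descriptive.
- **Mortality is covered elsewhere.** A reader might infer that the plan cannot see a mortality change. That is not so. Mortality at 90 and 180 days has its own survival analysis, and renal replacement dependency, ventilation, shock resolution and hospital stay are separate outcomes. What holds is narrower: this cut does not register a death averted into OCO 2-4.
- **Halved power is one reading.** The wording "Based on the assumption that the OCO group can be improved by at least 2 stages in 42% of IG patients" allows larger moves and a wider base, and the loss then shrinks. This stands, so the size must be given as a range.
- **A binary outcome is easy to read, and the planned shift is not proportional.** The cumulative odds ratios (1.49, 1.86, 2.25, 2.01) differ, so a common odds ratio averages unequal effects. All four favour the intervention, however, and the ordinal model keeps about 92% power despite this.

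**Conclusion.** The point holds as a cheap improvement to a supportive analysis; it is not an error in the confirmatory plan. Under the exact two-stage reading, the only cut named is the weakest of the four: it misses about two thirds of the planned improvements and has about 49% power against 92% for an ordinal analysis (41% against 80% with dropouts as OCO 5).

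These figures assume exact two-stage moves in 42% of OCO 3-5, two-sided 0.05 and no covariates; the effect of adjustment was not modelled. A reader might take the halving as a general result. It is not: the other readings give 85% against over 99%, and 81% against 97%, and the difference nearly vanishes if half or more of the OCO 4-5 movers reach OCO 1. The ordinal model is about as powerful or more so in every scenario examined, and does not depend on which improvements occur.

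**What to change.** In Statistical methods, and in the SAP:

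1. Make the adjusted supportive analysis a proportional-odds model on the five-level OCO, with arm, centre (the randomisation stratum), age, sex and baseline SOFA score. Report the common odds ratio with its 95% confidence interval, and describe it as the analysis of clinical outcome without the anti-infective component.
2. Keep binary splits only as a descriptive display of the odds ratios at all four cuts. This retains the easily read good-outcome figure and checks the proportional-odds assumption.

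The cost is a change of wording and one standard SAS procedure, with no additional data or patients and no change to the primary test. The small downside is the proportional-odds assumption. If the four odds ratios differ clearly, the common one should be read as an average and shown beside them.
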